#### Disease progression in patients who are not disease free at the end of protocol

The most sensitive measure of change is likely to involve a metric incorporating tumour size and number of lesions in the case of multiple metastases. There is evidence that CT-based volumetric assessment of metastases (seeded region growing method, slice-based segmentation or threshold-based segmentation) is more accurate for assessment of disease progression than the Response Evaluation Criteria In Solid Tumors (RECIST) V.1.1 method of largest axial diameter.^24^ It is acknowledged that although RECIST criteria provide an objective means of assessment of solid tumour response to treatment, there is a risk of interobserver bias.^25^ Further, RECIST criteria may be insufficient to assess response to treatment in patients with colorectal liver metastases treated by biological agents such as bevacizumab.^26^ Thus, disease progression at end of protocol will be assessed both by RECIST V.1.1 criteria and volumetric assessment.

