**Methods and analysis:**

Colorectal cancer with Synchronous liver-limited Metastases: an Inception Cohort (CoSMIC) is an inception cohort study of patients with a new diagnosis of colorectal cancer with synchronous liver-limited metastases. The sequence of treatment received, and factors influencing treatment decisions, will be evaluated against European Society of Medical Oncology guidelines. Clinical data will be collected, and quality of life, morbidity, mortality and long-term outcome compared for different treatment sequences adjusted for prognostic factors. Disease-free survival or progression will be measured at 1, 2 and 5 years. A nested qualitative study will ascertain patient experiences and clinician perspectives on delivery of care.

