#### Timelines for completion of the treatment protocol

For the purposes of this study, this is defined as the amount of time in days from enrolment to completion of the protocol. The term ‘protocol’ relates to completion of the common treatment pathway.

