#### Failure to complete the treatment protocol

This is defined as dropout prior to completion of the allocated treatment sequence. It will be further categorised as due to disease progression, patient choice or unrelated to colorectal cancer (for example myocardial infarction) and will be recorded as the time in days from enrolment.

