#### Disease-free survival 12 months after enrolment into protocol

This is defined as the absence of tumour on a CT scan of the thorax, abdomen and pelvis undertaken at the completion of the protocol. In the case of those patients with rectal tumours treated by a’ watch and wait ‘policy, the term disease free can only be applied if there is a combination of radiological, endoscopic and clinical evidence of absence of cancer.

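### The only working definition of disease progression is tied to pathway completion and residual disease, conflicts with the 1, 2 and 5 year schedule, and is not linked to treatment failures caused by progression

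*Protocol article*

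**What the plan says.** Four consecutive outcome definitions in the protocol article bear on this.

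- *Timelines for completion of the treatment protocol*: "The term ‘protocol’ relates to completion of the common treatment pathway".
- *Failure to complete the treatment protocol*: defined as "dropout prior to completion of the allocated treatment sequence". On cause, the section adds: "It will be further categorised as due to disease progression, patient choice or unrelated to colorectal cancer". The time in days from enrolment is recorded.
- *Disease-free survival 12 months after enrolment into protocol*: "absence of tumour on a CT scan of the thorax, abdomen and pelvis undertaken at the completion of the protocol".
- The progression section is headed "Disease progression in patients who are not disease free at the end of protocol". It concludes that "disease progression at end of protocol will be assessed both by RECIST V.1.1 criteria and volumetric assessment".

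Other parts of the article speak more broadly. The abstract says: "Disease-free survival or progression will be measured at 1, 2 and 5 years". Box 1 under *Data collection* lists disease-free survival and disease progression under the same three time points, and the *Dissemination policy* sets outcome data at those points. The *Analysis plan* says that every patient contributes outcomes, grouped by the sequence received.

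**The concern.** Comparing outcomes between synchronous and sequential surgery is a stated aim, and progression is one of the outcomes. The *Background* connects progression with the choice of sequence in both directions. It offers liver progression to unresectability as an argument for liver-first surgery, and it cites some evidence of worse progression-free survival after synchronous resection. Who enters the progression outcome therefore matters.

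The one section that says how and in whom progression is assessed has two features that could distort such a comparison. First, it is anchored to a point that a patient stopped by progression does not reach, so the clearest progression events fall under a different outcome. Second, its population, patients with residual disease at completion, is itself a result of treatment, so sequences would be compared in subgroups that treatment has shaped. *Acknowledgement of selection bias* recognises that progression selectively removes bowel-first patients before referral. The article says nothing comparable about loss after enrolment.

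The timing of the disease-free scan is a separate question and is not argued here.

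**Working it through.** **The plan's own figure.** The only size figure is in *Study size*: about 75 patients a year for 2 years, 75 × 2 = 150, which agrees with the stated 150. There is no power calculation, and no progression or dropout rate by sequence. All rates below are assumptions.

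**The passages side by side.**

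| Question | Four outcome definitions | Elsewhere |
|---|---|---|
| When is progression assessed? | End of protocol, i.e. pathway completion | 1, 2 and 5 years (abstract, Box 1) |
| In whom? | Those not disease free at that point | All patients (*Analysis plan*) |
| How is progression that stops treatment classed? | Failure to complete, with cause and day | No rule |

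The two columns are not reconciled, and nothing says whether a failure due to progression is also a progression event.

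**Illustration 1: omitting those stopped by progression.** Let T be total progression among all enrolled and d the share stopped by progression before completion, with no other losses. Among the rest, the observed proportion is (T − d)/(1 − d). Sequences A and B have the same T; only d differs.

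| T (both) | d, A v B | Observed, A v B | Spurious gap (points) |
|---|---|---|---|
| 30% | 5% v 15% | 26.3% v 17.6% | 8.7 |
| 30% | 5% v 25% | 26.3% v 6.7% | 19.6 |
| 30% | 10% v 30% | 22.2% v 0.0% | 22.2 |
| 40% | 5% v 15% | 36.8% v 29.4% | 7.4 |
| 40% | 5% v 25% | 36.8% v 20.0% | 16.8 |
| 40% | 10% v 30% | 33.3% v 14.3% | 19.0 |
| 50% | 5% v 15% | 47.4% v 41.2% | 6.2 |
| 50% | 5% v 25% | 47.4% v 33.3% | 14.0 |
| 50% | 10% v 30% | 44.4% v 28.6% | 15.9 |

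Example: (0.40 − 0.05)/0.95 = 36.8% and (0.40 − 0.15)/0.85 = 29.4%. The gap always favours B, which loses more patients to progression. B can even be truly worse and look better: with T = 35% v 45% and d = 5% v 25%, the observed values are 0.30/0.95 = 31.6% v 0.20/0.75 = 26.7%. Counting those stopped restores T exactly, since (1 − d) × (T − d)/(1 − d) + d = T.

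**Illustration 2: the literal denominator.** Illustration 1 divides by all completers, whereas the section heading is narrower (completers with residual disease). Assume 50 patients per group.

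- Sequence C: 10 stopped by progression; 10 complete with residual disease, of whom 4 progress. Literal: 4/10 = 40%. All enrolled: (10 + 4)/50 = 28%.
- Sequence D: 2 stopped by progression; 12 complete with residual disease, of whom 6 progress. Literal: 6/12 = 50%. All enrolled: (2 + 6)/50 = 16%.

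C looks better on the literal outcome and is worse among all enrolled.

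**The case against.** The strongest reply is that the article does not exclude anyone. Progression is also scheduled at 1, 2 and 5 years, all patients are to be analysed, failures due to progression are captured with cause and day, and mortality after enrolment is recorded. On this view the progression section only describes how residual disease is read. It states no proportion, no denominator and no test between sequences, and in a condensed article such details may sit in the full protocol or analysis plan.

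Much of this stands. A reader might infer that progression is measured only at end of protocol; the abstract and Box 1 contradict that. A reader might also infer that patients stopped by progression are lost to the study; the failure outcome and the *Analysis plan* contradict that.

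The reversal in Illustration 2 rests on invented counts and appears only if the progression outcome is read alone. In the same example, failures due to progression are 10/50 = 20% v 2/50 = 4%. Patients disease free at completion are (50 − 10 − 10)/50 = 60% v (50 − 2 − 12)/50 = 72%. Both of these outcomes rank the sequences correctly. *Study size* also expects few dropouts, and the analysis is described as exploratory and the reporting as descriptive.

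What does not stand is that nothing needs changing. The 1, 2 and 5 year statements carry no population or event rule, and the general statement about all patients does not amend a section whose heading restricts its population. Recording an event under one outcome does not place it in another. 'End of protocol' could have been meant as whenever treatment ends, but the article says it "relates to completion of the common treatment pathway", so that meaning would itself need a change of wording. This is text that the article states and leaves in conflict, rather than detail left to another document.

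**Conclusion.** The concern holds as an inconsistency with a consequence for bias. The only operational definition of progression is tied to pathway completion and residual disease. It conflicts with the 1, 2 and 5 year schedule and with the inclusion of all patients, and no rule links failures due to progression to the progression outcome. If sequences are compared on that definition as written, patients stopped by progression are omitted and the comparison conditions on a post-treatment subgroup. This can favour the sequence that loses more patients to progression.

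The size cannot be fixed from the documents. The 6 to 22 points rest on assumed total progression of 30–50%, assumed differences in progression dropout of 10 to 20 points, and no other losses. With similar or low dropout in all sequences, the effect from omission would be small. The documents do not support saying that the comparison will be reversed, only that the literal outcome would allow it.

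**What to change.** Reconcile the four outcome definitions with the abstract, Box 1, the *Analysis plan* and the *Dissemination policy*, as follows.

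- Define progression from enrolment, in all enrolled patients, at the stated 1, 2 and 5 year points.
- Count a failure to complete that is due to disease progression as a progression event on its recorded day.
- State how deaths without progression are handled. The choice is the study team's, but it should be written down.
- Keep the end-of-protocol RECIST V.1.1 and volumetric readings as a descriptive measure in patients with residual disease, not as the basis for comparing sequences.

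The cost is a change of wording and some extra derivation. The cause and day of failure are already recorded, so no additional scans are needed, and interim restaging scans need no RECIST reading. The reported progression rate may look less favourable, because it will include patients whom the literal definition does not reach. *Data sources and measurements* makes longer outcome collection, up to 5 years, contingent on separate funding; this change does not alter that.

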#### Resection margin status

The terms R0 bowel resection and R0 liver resection will be used (R0 means no tumour at or within 1 mm of surgical resection margin).^27 28^

#### Complication and treatment-related morbidity profiles

Complications will be recorded prospectively according to the criteria defined above (see treatments) and assessed at the end of the study. Operative outcomes will be reported in keeping with the Dindo-Clavien system of assessment of postoperative morbidity.^29^ The specific posthepatectomy complications of haemorrhage,^30^ bile leakage^31^ and liver failure^32^ will be recorded in compliance with the guidance of the International Study Group of Liver Surgery. The morbidity associated with each intervention step will be recorded separately. Morbidity will include unplanned readmission and reoperation. Requirement for non-elective surgery for colonic complications (obstruction, perforation, bleeding) will be recorded.

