### Recruitment

Patients will be formally identified prospectively at the weekly regional HPB MDT and approached in the outpatient clinic at MRI to discuss participation. Recruitment began in April 2015. For patients wishing to enrol, but where the treatment pathway has already started (typically those who presented with an acute abdomen secondary to the bowel lesion), data will be retrospectively collected on treatment already received. Missing data points, particularly quality of life prior to surgery, during data analysis will be compensated for by unit imputation.

Potential participants of qualitative study will be approached following completion of their treatment either in the outpatient clinic or by telephone to ascertain their interest in taking part in the interviews.

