### Data sources and measurements

Data will be collected prospectively using electronic study clinical case report forms. These will be anonymised and encrypted for storage and analysed prospectively during study to maximise data completion and resolve emergent problems in a timely fashion. The principal source of data will be the individual patient records. In addition, information will be gained by direct interview with patients (for quality of life assessment) and by interview with clinicians (for MDT choice decisions). Vital status beyond the duration of the study will be determined through the Demographics Batch Service of the NHS. Data will be reported at the end of year 3 allowing for a minimum 12 months outcome data in the entire cohort. It is also proposed (contingent on separate funding) that information on outcome will be collected for up to 5 years from study commencement, providing an informative survival analysis of treatment options.

Qualitative interviews will be audio recorded and transcribed verbatim.

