### Analysis plan

The care of patients within the study pathway will be characterised by their principal treatment route as synchronous, liver first or bowel first. All patients will provide outcomes which will be included within analyses, grouped according to the treatment sequence received. Complication profiles in patients according to treatment group will be reported.

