### Acknowledgement of selection bias

The liver metastases multidisciplinary team meeting at the Manchester Royal Infirmary is the sole forum approved by cancer commissioners for discussion of the care of patients with colorectal cancer liver metastases. The HPB unit guideline is that all patients with stage IV colorectal cancer should have their care reviewed at the MDT. However, it is acknowledged that there are several groups of patients who may bypass the MDT. In particular, patients with systemic disease ‘beyond liver’ may be referred for chemotherapy without consideration for liver surgery. From the patient’s perspective, this care pathway is appropriate. Similarly, patients who present to local MDTs with liver metastases who undergo bowel-first surgery but whose disease progresses rendering them unsuitable for consideration for liver surgery will likely not be referred. For the purposes of reporting the CoSMIC data, these sources of patient loss to study will be acknowledged together with any potential for selection bias. Reporting will be pragmatic and descriptive.

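### Complications are described as prospectively recorded, but operations before enrolment are captured retrospectively, mainly in bowel-first patients, so the profiles by sequence mix modes of ascertainment with a net bias of uncertain direction

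*Protocol article*

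**What the plan says.** The section on complication and treatment-related morbidity profiles says: "Complications will be recorded prospectively according to the criteria defined above (see treatments) and assessed at the end of the study". The section on data sources and measurements says the same of data generally: "Data will be collected prospectively using electronic study clinical case report forms". Neither makes an exception for treatment given before the patient joined the study.

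The Recruitment section does make one. For patients "where the treatment pathway has already started (typically those who presented with an acute abdomen secondary to the bowel lesion"), it says "data will be retrospectively collected on treatment already received".

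The Analysis plan classifies care as synchronous, liver first or bowel first and states: "All patients will provide outcomes which will be included within analyses, grouped according to the treatment sequence received". It adds: "Complication profiles in patients according to treatment group will be reported". No split by mode of capture is described. The abstract lists morbidity among the outcomes to be compared between treatment sequences.

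**The concern.** The prospective claim cannot hold for an operation that took place before enrolment. The exception also does not fall evenly. If the pathway typically began early because of an acute abdomen from the bowel lesion, the earlier operation will mostly have been on the bowel, and the patient will mostly be classed as bowel first. That is an inference from the Recruitment text, but a short one. Mode of ascertainment is then tied to the exposure under comparison.

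The Background section raises the morbidity of combined liver and bowel resection as a reservation about synchronous surgery, and the study is meant to guide later trials. A difference between sequences that comes from how or when events were captured could be read as a difference in surgical morbidity.

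The planned imputation of missing data would not help. A complication that nobody wrote down normally enters the dataset as no complication, not as a missing value. Adjustment for acuity is aimed at case mix. It would deal with recording only so far as acuity and timing of surgery coincide.

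**Working it through.** **The plan's own figure.** The only sample-size figure is 75 patients a year over 2 years: 75 × 2 = 150, as stated. The point does not depend on it. The documents give no complication rate, no share of patients operated on before enrolment and no completeness of capture.

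**Which events are affected.** Only operations before enrolment. A liver resection done after enrolment in the same bowel-first patient is captured prospectively. The liver-surgery-specific definitions of haemorrhage, bile leak and liver failure concern the liver step and so are largely untouched. The exposed items are Clavien-Dindo grades, readmission and reoperation for the earlier bowel operation.

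**Three mechanisms.**
1. *Recording.* Minor grades depend on what was noted at the time. In-study data checks, which the protocol introduces to maximise completion, cannot act when an event occurred before enrolment. This would lower the observed bowel-first rate.
2. *Survival to enrolment.* A patient has to survive an operation to be recruited after it. Box 1 lists 30-day mortality and the Mortality section counts deaths after enrolment. Operations before enrolment can therefore contribute essentially no grade V event or 30-day death; the exception is a patient who enrols and dies within the 30 days. This is selection, not poor abstraction, and it also lowers the bowel-first figure.
3. *Case mix.* Acute presenters may have a higher true complication risk, which raises the bowel-first rate.

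**Net direction of mechanisms 1 and 3.** Let p be the complication rate for bowel operations after enrolment, f the share of bowel-first operations done before enrolment, s the share of complications captured retrospectively relative to prospectively, and RR the risk of the earlier operations relative to the later ones.

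Observed bowel-first rate = p[(1 − f) + f·s·RR], so the shift = p·f·(s·RR − 1).

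All four inputs are assumptions: p = 35%, f = 20% to 80%, s = 60% to 90%, RR = 1 to 2.

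| RR | Lowest shift (points) | Highest shift (points) |
|---|---|---|
| 1.0 | −11.2 (f = 0.8, s = 0.6) | −0.7 (f = 0.2, s = 0.9) |
| 1.25 | −7.0 (f = 0.8, s = 0.6) | +3.5 (f = 0.8, s = 0.9) |
| 1.5 | −2.8 (f = 0.8, s = 0.6) | +9.8 (f = 0.8, s = 0.9) |
| 2.0 | +1.4 (f = 0.2, s = 0.6) | +22.4 (f = 0.8, s = 0.9) |

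For example, at RR = 1, f = 0.8 and s = 0.6: 0.35 × 0.8 × (0.6 − 1) = −0.112.

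The sign changes when RR exceeds 1/s: 1.67 at s = 60%, 1.33 at s = 75%, 1.11 at s = 90%. Modest excess risk in acute cases is enough to reverse the direction when capture is good. The model covers the bowel step only and leaves out mechanism 2.

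**The case against.** A reader might infer more than this: that bowel-first surgery is under-ascertained and will look safer than the other sequences. The documents do not support that, for four reasons.

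- Nothing in the text says retrospective capture is incomplete. For the whole cohort, "The principal source of data will be the individual patient records", so the contrast between prospective and retrospective capture is narrower than the labels suggest.
- The affected patients are typically acute presenters. As the table shows, their risk could make bowel-first surgery look worse.
- The selection-bias section refers to "patients who present to local MDTs with liver metastases who undergo bowel-first surgery", but the sentence goes on to say that those whose disease progresses beyond consideration for liver surgery are unlikely to be referred. It describes patients lost to the study, not poorly recorded complications in patients who are in it.
- Any size put on the bias is assumed throughout.

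The protocol also discloses the retrospective component, records morbidity for each intervention step separately, and calls its reporting descriptive and its modelling exploratory. A flag on the case report form is the kind of detail an article may leave to the full protocol.

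All of this stands, and it limits the point to unequal ascertainment of unknown direction. It does not remove it. The unqualified prospective statement is in the published text and is contradicted by the Recruitment section. Biases that may offset each other also make a comparison harder to interpret, not safer.

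**Conclusion.** The point holds in a limited form. The morbidity section's prospective claim is wrong for operations before enrolment, and these fall mainly in the bowel-first group, so the complication profiles by sequence rest on unequal ascertainment.

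Possible under-recording of minor events and survival to enrolment both lower the bowel-first figure, while higher risk in acute cases raises it. The net direction for complications overall is uncertain and the documents give no magnitude; the range in the table only shows that either sign is possible. For perioperative death the effect is clearer, since operations before enrolment are nearly free of it by construction.

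The conclusion assumes that treatment started before enrolment is mostly bowel surgery. This is an improvement worth making at low cost, not a flaw that undermines the cohort.

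**What to change.** 1. In the morbidity section, limit the word *prospectively* to operations after enrolment, and say that earlier operations are captured retrospectively, in line with the Recruitment section.
2. Flag each operation as before or after enrolment. Operation and enrolment dates give this, including for patients already recruited.
3. Report complication profiles by sequence separately for the two sets of operations, and add a between-sequence sensitivity analysis restricted to operations after enrolment.
4. Do not compare 30-day or grade V mortality between sequences using operations before enrolment.

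The cost is one derived field and a few sentences. The restricted analysis will contain fewer bowel-first operations and a less acute bowel-first case mix. It therefore answers a narrower question, and that should be stated where it is reported.
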